## Abstract

**Background:**

In recent decades, millions of people globally have taken up Buddhist spiritual and secularized meditation practices, such as mindfulness, with the aim of improving their quality of life and well-being. Practitioners are recommended to continue meditating regularly for the long term; however, the effects of regular meditation practice after introductory instruction remain scientifically underexplored.

**Objective:**

This protocol aims to investigate whether regular meditation practice improves quality of life and mental well-being and whether its effects vary between secular and spiritual practitioners. We will also explore the cost-effectiveness of meditation in terms of quality of life and the incidence and functional impact of any adverse effects associated with the practice.

**Methods:**

We will conduct a prospective longitudinal cohort study of 600 beginner meditators in Australia, New Zealand, the United States, and the United Kingdom over a 1-year period. Meditation practice frequency and duration will be reported weekly through the ambulatory assessment app Fabla (Emory University), with sampling of the primary outcome of quality of life and secondary outcome of mental well-being at monthly intervals. Practice characteristics, including secular versus spiritual practice, will also be reported monthly, as will the costs of meditation and mental health care and the incidence, severity, and duration of any adverse effects. Potential confounders, including baseline mental health symptoms, social support, and sociodemographics, will be controlled for in linear mixed models. An incremental cost-effectiveness ratio will be calculated, and sensitivity analyses will be conducted.

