Does regular meditation practice after initial instruction increase mental well-being?	The amount of meditation practice during approximately the first year predicts practitioners’ mental well-being, such that a greater amount leads to greater mental well-being.	A number of 242 gives 95% power to detect the variance in mental well-being (SWEMWBS^b^) explained by monthly meditation practice observed in linear mixed model analysis, at a 2-tailed significance level of 0.05, accounting for an estimated 20% loss to follow-up.	Linear mixed model of the fixed effect of the amount of meditation in the past month on mental well-being in the past 2 weeks (SWEMWBS), controlling for the confounding factors of age, caring status, education, mental health diagnosis, commitment to meditation, and membership of a practice support community at baseline.	A positive/negative and statistically significant association between the amount of meditation in the past month on mental well-being in the past 2 weeks will suggest that regular meditation practice after initial instruction increases/decreases mental well-being in a linear fashion. A nonsignificant association will suggest an absence of evidence for this.
Is the effect of continued meditation practice after initial instruction on quality of life moderated by whether a practitioner’s meditation tradition is spiritual or secular?	Whether the meditation tradition is secular or spiritual will moderate any effects on quality of life (nondirectional)	Sampling plan follows hypothesis 1, with an additional 20%, n=627, powered to detect effect of f^2^=0.0318	Linear mixed model of the fixed effect of the amount of meditation in the past month and the interaction effect of tradition spirituality on quality of life in the past week (EQ-HWB-9), controlling for the confounding factors of age, caring status, education, mental health diagnosis, commitment to meditation, and membership of a practice support community at baseline.	A positive/negative statistically significant beta coefficient for this interaction will indicate that regular meditation practice within a spiritual tradition will have a larger/smaller effect on quality of life than practicing within a secular tradition. A nonsignificant association will suggest absence of evidence for this.

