Is the effect of continued meditation practice after initial instruction on mental well-being moderated by whether a practitioner’s meditation tradition is spiritual or secular?	Whether the meditation tradition is secular or spiritual will moderate any effects on mental well-being (Hypothesis 4, nondirectional).	Sampling plan follows hypothesis 2, with an additional 20%, n=291, powered to detect effect of f^2^=0.045	Linear mixed model of the fixed effect of the amount of meditation in the past month and the interaction effect of tradition spirituality on mental well-being in the past 2 weeks (SWEMWBS), controlling for the confounding factors of age, caring status, education, mental health diagnosis, commitment to meditation, and membership of a practice support community at baseline.	A positive/negative statistically significant beta coefficient for this interaction will indicate that regular meditation practice within a spiritual tradition will have a larger/smaller effect on mental well-being than practicing within a secular tradition. A nonsignificant association will suggest absence of evidence for this.
What is the association between the costs and outcomes of meditation practice?	No hypothesis	Our sampling plan will follow hypothesis 1.	We will conduct an exploratory cost-effectiveness analysis to compare effects (quality of life) with a range of costs (costs of mental health support, costs associated with meditation practice)	Results will be presented as an ICER^c^ with associated sensitivity analysis, as outlined above.
What is the incidence and functional impact of meditation-related adverse effects	No hypothesis	—^d^	Proportion and CIs of the frequency, severity of impairment on daily function, and duration of impairment of initial meditation-related challenging experiences and adverse effects (MRAEs)	—

a EQ-HWB-9: 9-item EuroQoL Health and Wellbeing.

b SWEMWBS: Short Warwick-Edinburgh Mental Well-Being Scale.

c ICER: incremental cost-effectiveness ratio.

d Not applicable.

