### Participant Verification

The study uses a combination of methods to both discourage nongenuine participants and to verify that those participants who are recruited are genuine. Entry into the study involves 4 Qualtrics surveys delivered on consecutive days, followed by download of the app Fabla, which is restricted to Australia, New Zealand, the United Kingdom, or the United States, before commencing the weekly survey schedule, as shown in Table 3. The first expression of interest survey will exclude participants who fail Qualtrics internal bot checks and who are detected to be outside our recruitment countries. The second survey will repeat date of birth questions from the expression of interest to detect inconsistent responses.

**Table 3. T3:** Schedule of measures.

Measures	Baseline	Weekly	Monthly	1 year
Outcome measures				
Health and well-being (EQ-HWB-S^a^)	✓		✓	✓
Mental well-being (SWEMWBS^b^)	✓		✓	✓
Independent variables				
Meditation practice frequency and duration		✓		
Meditation practice characteristics	✓		✓	✓
Secular or spiritual practice tradition	✓		✓	✓
Covariates				
Meditation history	✓			
Sociodemographics	✓			
Physical and mental health status	✓			✓
Other variables				
Cost of meditation practice	✓		✓	✓
Cost of mental health care use	✓		✓	✓
Meditation-related adverse effects scale (MRAES)	✓		✓	✓

a EQ-HWB-S: EQ Health and Wellbeing—Short version.

b SWEMWBS: Short Warwick-Edinburgh Mental Well-Being Scale.

After we have received 7 separate survey responses from participants, their IP and internet service provider (ISP) will be inspected. This IP inspection identifies participants whose IP addresses change on each survey, which indicates possible “residential proxy” use, those who have IP addresses associated with a known virtual private network (VPN), those who have more than 2 ISPs associated with their IPs, and those who have IP addresses associated with a data center (eg, Amazon Web Services).

Participants who are identified by these IP inspections will be manually screened by listening to voice recordings they will provide in Fabla. Those participants who we are not able to verify through this process will be contacted and offered an online interview. Prospective participants who do not respond after follow-up, refuse an interview or alternative contact method, or are suspected to be nongenuine during an interview will be considered nongenuine, excluded from further participation, and have their data removed.

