### Sampling Plan

#### Hypothesis 1

Sample size calculation for quality of life measured by the EQ-HWB-9 using repeated measures linear mixed modeling assumes three groups will be assessed with (1) low, (2) medium, and (3) high regular meditation dosage. Given the limited research on the effects of long-term regular meditation practice, calculating power is challenging. We have therefore used conservative power calculations that may err on the side of underestimating the power of our primary analysis but allow for use of the effect information and analytic tools that are available. We have conducted power analysis using 3 levels of variation in the predictor of monthly meditation amount, rather than the continuous variable we plan to use in our final analysis. This is to allow for the use of an analytic power calculation method for our repeated measures design, rather than simulation measures, which would be highly speculative with the limited real and independent data available for our outcome measure [64]. Ten measurement time points were also used, rather than the 12 that will be included in our analysis, as this is the maximum for GLIMMPSE (University of Florida and University of Colorado Denver) power analysis software [65].

Sample size calculation for quality of life measured by the EQ-HWB-9 using repeated measures linear mixed modeling assumes three groups will be assessed with (1) low, (2) medium, and (3) high regular meditation dosage. No increase in EQ-HWB-9 scores was predicted for the low meditation group [58]. For the high meditation group, we estimate a stepwise increase to a minimum of a 2.25-point EQ-HWB-9 increase (out of a possible 9‐45 points) from baseline to time point 5, corresponding to the change in EQ-HWB-9 from baseline to 6 months associated with improvement in mental health in a validation of the EQ-HWB-9 sensitivity to change [59]. We then predict a further 2.25-point increase to time point 10, for a total increase of 4.5 points. For the moderate meditation group, stepwise improvement was predicted with a minimum of a 2.25-point EQ-HWB-9 increase from baseline to time point 10. Baseline EQ-HWB-9 is set at 19.6, with an SD of 7.0, as per our nationally representative surveys [66]. Using GLIMMPSE [65] with 95% power and 0.05 2-tailed type 1 error rate, sample size was calculated at 435 participants. We estimated a 20% loss to follow-up over one year, bringing the sample size required to 522 participants.

#### Hypothesis 2

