There is limited research investigating whether meditation practice being spiritual or secular moderates the effect of practice time. Previous studies have shown evidence that engaging in regular spiritual mind-body practices may moderate the effect of an initial meditation program at 6 months, such that stress and depressive symptoms are only improved compared to treatment as usual for those individuals who do not regularly engage in spiritual mind-body practices [67]. However, this was not compared to similar secular meditation practices. Our prospective longitudinal study found that those with a spiritual goal for meditation practice obtained less benefit from their meditation practice for life satisfaction and positive affect [32]. Nevertheless, to our knowledge, the moderating effect of practicing within a spiritual tradition on quality of life or well-being as outcomes is yet to be investigated or observed over a one-year follow-up. Therefore, potential effect sizes for these analyses are highly uncertain. As such, to account for testing these hypotheses, we plan to increase our sample by an additional 20% from what is required for power to test our primary outcome (Hypothesis 1) to 627 participants. With this sample and our planned model, setting power to 0.95 and significance to 0.05 2-tailed, we will be powered to detect a moderation effect of f^2^=0.0352 [68].

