## Results

The protocol for this study was preregistered on May 9, 2024 [73] (embargoed). This manuscript was originally submitted on October 1, 2025. We soft-launched to test our systems on October 28, 2025, and initiated substantial recruitment efforts in January 2026. As of May 14, 2026, 341 participants have completed baseline measures. We expect to complete data collection and publish results in January 2028.

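### The abstract gives a cohort of 600, but the sampling plan and Table 1 set 627 for the moderation test on quality of life and base its detectable effect on 627

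*Protocol article*

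**What the plan says.** The Methods paragraph of the abstract plans a "prospective longitudinal cohort study of 600 beginner meditators".

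The Sampling Plan builds up a different number. For Hypothesis 1, "sample size was calculated at 435 participants", and a 20% allowance for loss to follow-up brings this to 522. For Hypotheses 3 and 4 the authors say that likely moderation effects are highly uncertain, and that they will therefore "increase our sample by an additional 20% from what is required for power to test our primary outcome (Hypothesis 1) to 627 participants". They then give f² = 0.0352 as the moderation effect detectable with that sample, at 95% power and two-sided 5% significance.

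Table 1 repeats the size for Hypothesis 3 with a different detectable effect: "Sampling plan follows hypothesis 1, with an additional 20%, n=627, powered to detect effect of f^2^=0.0318". For Hypothesis 4 it says: "Sampling plan follows hypothesis 2, with an additional 20%, n=291, powered to detect effect of f^2^=0.045".

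The Results section reports progress: "As of May 14, 2026, 341 participants have completed baseline measures". Under Participant Verification, IP inspection follows seven survey responses. People who then cannot be verified are "considered nongenuine, excluded from further participation, and have their data removed".

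**The concern.** One cohort has two planned sizes. If recruitment stops at 600, the team has done what the abstract says and missed what the Sampling Plan says; at 627 the reverse holds. Either stopping point could later be described as the planned one. Recruitment was still open at the last report, so the question is live.

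The difference reaches a stated operating characteristic. The article ties its detectable moderation effect to 627, so that figure does not describe a study of 600.

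**Working it through.** **Inputs.** 600 (abstract, Methods); 435, 20% loss and 522 (Sampling Plan, Hypothesis 1); 201 and 242 (Sampling Plan, Hypothesis 2); 627, f² = 0.0352, power 0.95 and two-sided alpha 0.05 (Sampling Plan, Hypotheses 3 and 4); 627 with f² = 0.0318, and 291 with f² = 0.045 (Table 1).

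**Step 1: reproduce the plan's sizes.**
- Hypothesis 1: 435 × 1.2 = 522.
- Hypothesis 3: 522 × 1.2 = 626.4, rounded up to 627.
- Hypothesis 2: 201 × 1.2 = 241.2, rounded up to 242.
- Hypothesis 4: 242 × 1.2 = 290.4, rounded up to 291.

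All four reproduce. The 435 itself was not recomputed, because the covariance inputs are not given; nothing here depends on it. The figure of 600 follows from no stated step.

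**Step 2: compare 600 with the stated uplift.**
- 600 / 522 = 1.149, so the margin over Hypothesis 1 is 14.9%, not 20%.
- 627 − 600 = 27, and 27 / 627 = 4.3%.

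**Step 3: reproduce the stated detectable effects.** The method is a noncentral F test with noncentrality λ = f² × N, numerator degrees of freedom u, denominator N − u − 1, alpha 0.05 and power 0.95. The article does not state u, so it was found by matching.
- N = 627, u = 7 gives f² = 0.0352, the value in the text.
- N = 627, u = 5 gives f² = 0.0318, the value in Table 1.

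Both published values therefore match a calculation on all 627 participants with no attrition.

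**Step 4: repeat at 600.** The last row tests the single interaction term, with eight predictors in the model (denominator N − 9).

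| Basis | Detectable f², N = 627 | Detectable f², N = 600 | Power at N = 627 | Power at N = 600 |
|---|---|---|---|---|
| u = 7 (text) | 0.0352 | 0.0368 | 95.0% for 0.0352 | 93.9% for 0.0352 |
| u = 5 (Table 1) | 0.0318 | 0.0333 | 95.0% for 0.0318 | 94.0% for 0.0318 |
| u = 1 (single interaction term) | 0.0208 | 0.0217 | 99.7% for 0.0352 | 99.6% for 0.0352 |

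**Step 5: check the other hypotheses at 600.** 600 exceeds 522 (Hypothesis 1), 242 (Hypothesis 2) and 291 (Hypothesis 4). After 20% loss, 600 × 0.8 = 480, which is above the 435 needed for Hypothesis 1 and the 201 needed for Hypothesis 2. Only the size stated for Hypothesis 3 is missed.

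**Step 6: order of baseline and verification.** In Table 2 the baseline survey is the third contact, after the expression-of-interest survey and the consistency check. IP inspection needs seven responses, so it and any resulting removal of data come after baseline.

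**The case against.** The strongest reply is that 600 is a rounded figure in an abstract, that the Sampling Plan governs, and that the difference hardly matters. Much of this stands. The 627 comes from a flat 20% uplift and not from an assumed moderation effect, so 600 falls short of no calculated requirement for Hypothesis 3. About one point of power is lost on the article's own basis, and almost none if the test is of the single interaction term. The gap between the article's two values for the same 627 (0.0352 and 0.0318) is larger than the shift caused by moving to 600. What does not stand is leaving both numbers in place: the article never says that 600 is a rounding, and its detectable effect is tied to the other number.

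A reader might go further. Because progress is reported at baseline and nongenuine records are deleted later, the target might seem to be a gross count at baseline, with no replacement, so that the study must fall short of its stated size. The document does not support this. The 341 is a progress report and does not define how 600 or 627 is counted. The verification section calls those who fail it prospective participants, which is compatible with counting only verified people. Bot, location and consistency checks already precede the baseline survey. Replacement is a detail that an article commonly leaves to the full protocol. No removal rate is given, so no size can be put on any such shortfall.

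**Conclusion.** The inconsistency between 600 and 627 is real, and it is minor. It touches the stated size and detectable effect for Hypothesis 3 only, raising the detectable f² by 0.0016 on the text's basis or 0.0015 on Table 1's. These figures assume that the published effects come from a noncentral F calculation on the full sample with 7 or 5 numerator degrees of freedom; the article does not state this, but both values reproduce under it. How the target is counted relative to verification is a point to clarify and not a demonstrated error.

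**What to change.** State one recruitment target in the abstract, the Sampling Plan and Table 1. If it is 627, correct the abstract. If it is 600, give 600 as the Hypothesis 3 size, describe the margin over 522 as about 15%, and restate the detectable effect for 600: 0.0368 on the text's basis or 0.0333 on Table 1's. Use the same basis in both places.

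As a clarification, add a sentence saying whether the target counts participants who have passed verification, since the IP check and any removal of data come after baseline.

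The cost is wording and, if 600 is kept, one slightly less favourable figure. No enrolment beyond the chosen target and no change of design is needed.

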**Results:**

Data collection began on October 28, 2025, after this study was first submitted on October 1, 2025. As of May 14, 2026, 341 participants have completed baseline measures. We expect results to be published in January 2028.

**Conclusions:**

Results of this investigation will illuminate the impact of meditation as it is currently practiced in natural contexts, and inform clinicians about whether and how regular meditation may be an effective tool for improving quality of life.

## Introduction

### Background

In the past few decades, millions of people globally have taken up Buddhist-inspired forms of meditation practice, either as a spiritual practice within a traditional setting or as a secular practice within contemporary contexts [1]. Whether the context is spiritual or secular, supporting health and well-being is one of the main aims among those practicing meditation [1-3]. In Buddhist traditions, meditation is considered a lifetime pursuit that requires years of prolonged practice to accumulate tradition-specific insights [4] and thus achieve greater quality of life in a contemporary sense. Buddhist-inspired secularized meditation programs have become increasingly popular as a tool for promoting quality of life and well-being [5]. The most prominent examples of these are mindfulness-based programs (MBPs), which typically offer introductory courses lasting several weeks, including a near-daily home-based practice component, and which encourage practitioners to continue regular practice indefinitely to maintain and strengthen quality of life and well-being [6,7]. An estimated half of the practitioners follow the recommendation and continue their practice regularly beyond course completion [8,9]. However, the effects of regular meditation practice after introductory courses remain much less explored than the effects immediately following the intervention training [10]. With millions of practitioners globally, it is imperative to understand the effects of regular meditation practice for improving quality of life beyond the initial instruction and whether it is a safe and economically viable intervention over time.

### The Current Evidence

There is strong evidence supporting the immediate effects of secular MBPs on quality of life and mental well-being [11-14]. Several longitudinal studies have also assessed whether salubrious effects persist after course completion. Some suggest maintained benefits after as long as 4 years [9,15-17]; however, others have reported decreased benefits over one and 3 years [18,19]. While benefits of MBPs may be long-lasting, it is unclear whether they can be attributed to continued meditation practice, given that most longitudinal studies have not monitored whether the participants continued their practice beyond the instruction period. Findings from some clinical populations have indicated a decrease in the frequency [20] and duration [21] of home practice over follow-up periods of 1-12 months post-MBP.

Mixed preliminary evidence of a relationship between meditation practice and well-being has been found in randomized controlled trials (RCTs) and longitudinal studies that measured meditation practice following MBPs. Our RCT assessing the effects of an MBP on university students’ mental well-being found improvement postintervention [22] and up to a year later [23], compared with a passive control group. This trial tracked meditation practice after course completion and found that benefits increased with practice [23]. In another longitudinal study, students’ practice of mindfulness skills was positively associated with better mental well-being 3 months after the MBP [24]. On the other hand, a meta-regression failed to show evidence that longer or more intense MBPs predict better psychological outcomes [25]. A study with a 4-year follow-up also found continued practice in mindfulness meditation was not related to mental well-being [17]. However, continued practice was measured by a question at follow-up, rather than by tracking the amount of meditation over the intervening period. To appropriately assess the effect of meditation practice on long-term well-being outcomes, a longitudinal study that regularly and accurately assesses the amount of meditation practice is needed.

